### Clinical outcomes

Clinical outcomes include information regarding the possible effects and safety of acupuncture. The outcome measures regarding clinical effect will be assessed at baseline, week 3, week 5, and week 9. A Visual Analogue Scale (VAS) score for the four major somatic symptoms and two major psychological symptoms of HB will be the primary outcome measure. The major symptoms are chest discomfort, burning sensation of the face or chest, a surge of feeling, sensation of a mass in the throat or in the epigastrium, frequent feelings of unfairness and mortification, and emotional resentment or ill will.

The VAS is widely used for the assessment of variations in the severity of subjective symptoms. Participants mark their symptom severity on a 100-mm straight line whose extreme left end indicates “absence of symptoms” and whose extreme right end indicates “unbearably severe symptoms” [33, 34].

The secondary clinical outcome measures will be the VAS score for subjective anger, the BDI and the short-form of the Stress Response Inventory (SRI-short form). The IOME-HB and serum serotonin levels will be evaluated at baseline and week 5. The BDI is a self-reported inventory to evaluate the severity of depression with 21 questions, including somatic-affective and cognitive-affective factors. Each question is assigned one of 0 to 3 points, and the total score ranges from 0 to 63 [35, 36]. The SRI-short form is used to assess responses to stress. It contains 22 questions, including somatization factors (nine items), depression factors (eight items), and anger factors (five items) [37]. The IOME-HB is used to evaluate the severity of psychiatric and somatic symptoms of each of five types of HB, according to TKM principles, by participants scoring their symptoms using a 5-point Likert scale [4, 5]. Serum serotonin levels will be measured by analyzing the blood drawn from the veins of the arm. We will quantitatively analyze the numbers themselves to see whether there are differences before and after treatment and between groups.

The follow-up evaluation will be performed 4 weeks after the completion of the treatment and will include the VAS for core symptoms, VAS for subjective anger, and the BDI and SRI-short form. To remind participants and encourage their participation in the follow-up assessment, we will inform participants about their visits by phone 1 to 7 days prior to the follow-up visit. Adverse events (AEs) will be recorded at every visit to assess the safety of the trial. The Standard Protocol Items: Recommendations for Interventional Trials (SPIRIT) schedule of enrollment, interventions, and assessments is shown in Fig. 2. The SPIRIT Checklist can be found in Additional file 2.

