## Characteristics of participants

### Inclusion criteria

Men and women who are aged 20 to 65 yearsMeet the diagnostic criteria of the HBDIS: participants should have at least three of the four major symptoms (including chest discomfort, burning sensation of the face or chest, a surge of feeling, and sensation of a mass in the throat or in the epigastrium), one of two major psychological symptoms (including feelings of unfairness and mortification, and emotional resentment or ill will), two of four related somatic symptoms, and two of three related psychological symptoms. The symptoms should be related to stress, should cause psychosocial hypo-function, and should not be caused by a medical disorderProvide written informed consent after being informed of the objectives and details of the clinical trial and agreeing to participate in the trial

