## Outcome measure

### Feasibility outcomes

We will evaluate the feasibility of the study by assessing recruitment, compliance, and completion rates. Acceptability of acupuncture will be also evaluated by investigating effect and safety. The acupuncture treatment will be regarded as an acceptable intervention for a full-scale study if the effect size is greater than 0.2 in at least three of six major symptoms. With respect to safety, a full-scale study will be planned if there is no serious adverse event (SAE) associated with the intervention and if the incidence of adverse events (AEs) is not significantly different from the CG.

The integrity of the study will be examined as a qualitative indicator with regard to whether the study proceeds without any problems and whether a full-scale study is possible without modification of the pilot study design. This will be measured using the Acceptance Checklist for Clinical Effectiveness Pilot Trials (ACCEPT) [31]. We will check the blinding index to determine whether the blinding procedure requires modification. The blinding index ranges from − 1 to 1, with 0 being the most favorable blindness level [32].

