### Statistical analysis

The recruitment rate, compliance rate, and completion rate will be presented as a number and percentage and will also be presented for each group. For clinical outcomes, including VAS scores for the core symptoms of HB and subjective anger, the BDI, the SRI-short form and serum serotonin levels, the mean SD at each assessment point and Cohen’s *d*, which is an estimated effect size that indicates the standardized difference between two mean values, will be presented [38]. Effect size will be calculated based on the value immediately after the end of the 4-week treatment (visit 10).

Analyses will mainly be performed using the full analysis set (FAS) population, while the per-protocol set (PPS) population will be analyzed as a supplement. Although the intention-to-treat (ITT) ideal includes all randomized subjects, the FAS approach acknowledges the practical infeasibility of completely following all participants until study completion and includes as complete and as similar a population to ITT as possible [39]. The FAS population does not include the following: (1) individuals who do not meet the inclusion criteria, (2) individuals who have never undergone acupuncture treatment, and (3) individuals who have never been assessed since randomization and, therefore, have no data available for collection. The PPS population will include the following: (1) individuals for whom acupuncture accounts for more than 80% of the total number of treatments received, (2) individuals who have had their evaluation parameters measured, and (3) individuals who do not violate the clinical trial protocol [40]. Missing data will be replaced by multiple imputation. Statistical analyses will be conducted by an independent statistician using SAS® version 9.4 (SAS Institute Inc., Cary, NC, USA).

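### Eligible participants may lack up to two of the six symptoms in the primary outcome, so the unadjusted single-symptom effect sizes behind the acceptability criterion are pulled toward zero by an unknown amount

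*Protocol article*

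**What the plan says.** Under Inclusion criteria, the diagnostic interview (HBDIS) sets the entry rule: "participants should have at least three of the four major symptoms" and "one of two major psychological symptoms", plus related symptoms that are not part of the primary outcome. No minimum VAS is required.

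Under Clinical outcomes, "A Visual Analogue Scale (VAS) score for the four major somatic symptoms and two major psychological symptoms of HB will be the primary outcome measure". These are the same six symptoms, each rated on a 100-mm line whose left end means that the symptom is absent.

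Under Feasibility outcomes, acupuncture counts as acceptable for a full-scale study "if the effect size is greater than 0.2 in at least three of six major symptoms".

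Under Statistical analysis, the measure is Cohen's d, "which is an estimated effect size that indicates the standardized difference between two mean values, will be presented". I read this as the difference between the two groups. On timing: "Effect size will be calculated based on the value immediately after the end of the 4-week treatment (visit 10"). The full analysis set is the main population. It has three exclusions, and none of them concerns a symptom that the participant did not have at entry.

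**The concern.** The entry rule and the outcome use the same six symptoms, but the rule does not require all six. For any one symptom, the analysed sample can therefore mix people who have it with people who rate it at or near zero before and after treatment. The second group has little or no room to improve, so the mean difference shrinks, and their distance from the rest adds between-person variance. Because d uses end values without adjustment, a chance difference between arms in how many people have the symptom also enters d directly.

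At stake is the acceptability criterion. It is judged symptom by symptom against a low threshold in about 13 participants per arm, and it helps decide whether a full trial goes ahead.

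**Working it through.** **Entry patterns.** Somatic symptoms: all four, or any one of four missing, gives 1 + 4 = 5 patterns. Psychological symptoms: both, or either one alone, gives 3 patterns. So 5 × 3 = 15 patterns qualify: 1 with nothing missing, 4 + 2 = 6 with one missing, and 4 × 2 = 8 with two missing. A participant can lack at most two of six.

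**Ceilings.** If every participant met the rule at its bare minimum, average absence would be 1/4 = 25% across the somatic symptoms and 1/2 = 50% across the psychological ones. These are upper limits on the averages, not expected values.

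**Dilution of d.** Let a share q of both arms score 0, and let the rest have mean μ, SD s and treatment difference δ.

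- Mean difference in all participants: (1 − q)δ
- Variance: (1 − q)(s² + qμ²)
- Diluted d / undiluted d = √[(1 − q) / (1 + q(μ/s)²)], which is below 1 for every q > 0

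The article gives no VAS mean or SD, so a range is needed. For μ/s from 1 to 2.5 the ratio is:

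| q | ratio |
|---|---|
| 10% | 0.90 to 0.74 |
| 25% | 0.77 to 0.54 |
| 50% | 0.58 to 0.35 |

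Worked example (assumed means 50 and 40 mm and SD 20 among those with the symptom, so d = 0.50). The average of 50² and 40² is 2,050.

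- q = 25%: 7.5 / √(0.75 × 400 + 0.1875 × 2,050) = 7.5 / √684.4 = 0.29
- q = 50%: 5 / √(0.5 × 400 + 0.25 × 2,050) = 5 / √712.5 = 0.19

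**SD.** The mixture SD exceeds s only if μ/s > 1/√(1 − q), which is 1.15 at 25% and 1.41 at 50%. At μ/s = 1 it is smaller than s, by factors of 0.97 and 0.87.

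**The three-of-six criterion.** This was simulated with 13 per arm, correlation 0.5 between symptoms (assumed), scores bounded at 0 and 100, and absences spread evenly within each symptom group.

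| Setting (assumed) | No absence | Half lack one somatic, half (independently) one psychological | Ceiling |
|---|---|---|---|
| Means 50/40, SD 20 (d = 0.5) | 88% | 81% | 76–77% |
| Control mean 50, SD 25, d = 0.5 | 87% | 82% | 79% |
| Same, d = 0.2 | 58% | 52% | 48% |
| Same, d = 0.8 | 98% | 96% | 95% |
| Same, d = 0 | 33% | 30% | 28% |

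For scale, the standard error of a single d at 13 per arm and d = 0.2 is √(2/13 + 0.04/52) = 0.39.

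**Alternatives at the ceiling** (SD 20 setting):

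- Restricting each symptom to those who had it at baseline brings the chance of passing under a true effect back to about 88%. With no effect, it raises that chance from 27% to 37%, because n per symptom drops.
- The baseline-adjusted mean over the symptoms present exceeds 0.2 in about 89% of runs under the same true effect, against 76–77% for the current criterion. With no effect it does so in about 28–29%, close to the current criterion's 27–28%. This assumes a correlation of 0.5 between baseline and end-of-treatment scores.

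**The case against.** The strongest reply is that this is a choice of target. The effect on each core symptom in everyone who meets the diagnosis is a legitimate descriptive quantity, it captures symptoms that emerge later, and the pilot disclaims hypothesis testing. No two statements in the article contradict each other. All of that stands. What remains is that the same values drive a stated pass mark, and the article itself fixes the population, measure, time point and threshold.

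Four further objections also stand and limit the point:

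- The criteria permit absence but do not force it, and no symptom frequency is given.
- Failing an interview item is not the same as marking 0 mm at both times. A reader might infer that such participants cannot improve at all, but the article says only that the left end of the line means absence. Low non-zero scores would soften the effect.
- For one symptom in the SD 20 example, the chance of d > 0.2 falls from 79% to 60% (25% absent) and 49% (50% absent). A reader might carry that drop over to the decision. The criterion needs only three of six symptoms, so its loss is smaller.
- Sampling error in d at this sample size is a larger problem for the criterion than dilution.

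**Conclusion.** The point holds in a limited form. Any participants at or near zero for a symptom they lack bias that symptom's d toward zero, and the planned analysis, as described, does nothing about it. The direction follows from the algebra. The size rests on assumed frequencies, means, SDs and correlations. In the d = 0.5 settings the criterion loses about 5 to 12 percentage points, the upper end only if every participant lacks the maximum.

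Three stronger readings are not supported:

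- **That the SD is always inflated.** This depends on μ/s, which the documents do not give.
- **That the all-participant SD would mislead the full trial.** The Discussion says that the pilot is set up to resemble the later trial. If that trial keeps the same entry rule and outcome, it has the same mixture, and the all-participant mean and SD are the right planning input.
- **That imbalance in who has a symptom makes a false pass more likely.** With no effect, the chance of passing falls slightly with absence (33% to 28%). The imbalance adds noise to individual estimates but does not raise the criterion's error.

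**What to change.** While the trial is still recruiting, and before any unblinded analysis, prespecify the following:

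1. For each participant, the mean VAS over the symptoms present at the baseline HBDIS, with a between-group effect size adjusted for the same mean at baseline. Base the acceptability judgement on this value and state its threshold.
2. The six single-symptom effect sizes in all participants, each adjusted for its own baseline VAS.
3. As supplementary only, each single-symptom d among those with the symptom at baseline, with n and a confidence interval. This subset is defined before randomization, so the comparison stays fair, but its smaller n makes chance values above 0.2 more likely.
4. The all-participant mean and SD as the planning input, if the full trial keeps the same entry rule.

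The cost is modest analysis work. Baseline VAS and the interview are already collected, provided that the interview results are kept item by item. There are two downsides. The composite misses symptoms that newly emerge. A mean of several symptoms also has a smaller SD than one symptom: with six symptoms, SD 20 and correlation 0.5 it is 20 × √(3.5/6) = 15.3 mm. A threshold of 0.2 then corresponds to about 3.1 mm instead of 4 mm, so the threshold should be chosen deliberately and not simply carried over.

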**Fig. 2 Fig2:**
[figure not shown]
The Standard Protocol Items: Recommendations for Interventional Trials (SPIRIT) Figure. The schedule of enrollment, interventions, and assessments

### Criteria for dropout

The subject or the legal representative of the subject withdraws their participationA violation of the inclusion/exclusion criteria is found during the course of the clinical trialThe development of an SAE or an AE causes difficulty in continuingLess than 80% compliance with the treatmentThe subject violates the plan of the clinical trialFailure to track the subjectThe subject takes medications that affect the results during the study period

### Data collection, management, and personal information protection

Data will be collected by the KMD who will be in charge of the questionnaire and evaluation. The KMD will have six or more years of specialized education and four or more years of clinical experience and will complete a workshop on evaluation standardization. Soft copies will be saved on a storage device not connected to the Internet. All data will be kept in locked storage, and only those with permission from the PI will be able to access the data. All blood samples will be disposed of immediately after they are analyzed. All retained data will contain codes to identify patients instead of personal information.

### Statistical analysis

The recruitment rate, compliance rate, and completion rate will be presented as a number and percentage and will also be presented for each group. For clinical outcomes, including VAS scores for the core symptoms of HB and subjective anger, the BDI, the SRI-short form and serum serotonin levels, the mean SD at each assessment point and Cohen’s *d*, which is an estimated effect size that indicates the standardized difference between two mean values, will be presented [38]. Effect size will be calculated based on the value immediately after the end of the 4-week treatment (visit 10).

Analyses will mainly be performed using the full analysis set (FAS) population, while the per-protocol set (PPS) population will be analyzed as a supplement. Although the intention-to-treat (ITT) ideal includes all randomized subjects, the FAS approach acknowledges the practical infeasibility of completely following all participants until study completion and includes as complete and as similar a population to ITT as possible [39]. The FAS population does not include the following: (1) individuals who do not meet the inclusion criteria, (2) individuals who have never undergone acupuncture treatment, and (3) individuals who have never been assessed since randomization and, therefore, have no data available for collection. The PPS population will include the following: (1) individuals for whom acupuncture accounts for more than 80% of the total number of treatments received, (2) individuals who have had their evaluation parameters measured, and (3) individuals who do not violate the clinical trial protocol [40]. Missing data will be replaced by multiple imputation. Statistical analyses will be conducted by an independent statistician using SAS® version 9.4 (SAS Institute Inc., Cary, NC, USA).

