Acupuncture has been used for various psychiatric disorders [16], and its clinical effect against depression [17] and anxiety [18, 19] has been reported in previous studies. For studies on HB, one study reported improvement in the symptoms of HB and Beck Depression Inventory (BDI) score but not in STAXI and State-Trait Anxiety Inventory (STAI) scores [20]. Several studies reported contrasting results, and did not find significant improvement in symptoms of HB or in BDI, STAXI, or STAI scores [21, 22]. These three studies included a control group that received shallow, penetrating, sham acupuncture at non-acupuncture points, which may have contributed to a failure to detect differences between the groups. In addition, the acupuncture used in these studies was focused on traditional eastern philosophy using the Five Elements Theory; thus, the method exhibited limitations in the possible widespread use by global researchers and practitioners. Two studies focused on concurrent symptoms, such as insomnia and anxiety, but remained limited in that one used a waiting list and the other included a single-group, open-trial design [23]. In 2013, clinical guidelines for HB were developed encompassing various studies. The guidelines indicated the limitations as a standardized treatment regimen could not be determined. The clinical guidelines proposed the use of acupuncture to treat HB based on previous evidence and noted that individualized treatment that considers the specific disposition and level and type of stress must be simultaneously provided [24]. Given the need for further research regarding individualized treatment, the present clinical study protocol was developed to use both fixed acupuncture points related to the major symptoms of HB, and variable acupuncture points based on traditional Korean medicine (TKM) principles.

Accordingly, we designed a randomized, sham-controlled, participant- and assessor-blinded, parallel-design pilot study using sham-treatment control and a 1:1 allocation. We will assess the clinical trial feasibility, and explore the effect and safety of acupuncture as a treatment for HB by comparing an experimental group (EG) receiving semi-individualized acupuncture with a control group (CG) receiving sham acupuncture.

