### Sample size calculation

This study aims to evaluate clinical trial feasibility and to investigate basic information about effects and safety of acupuncture for the treatment of HB, rather than to satisfy hypothesis testing. Therefore, the sample size was not decided based on power calculations but based on the precision of mean and standard deviation (SD), the rationale of feasibility, and ethical issues that prohibit over-recruitment of participants. We ensured that the sample size exceeded the minimal number needed to assure the validity of the mean, SD and effect size and rationale of feasibility [25] and considered the study period and research budget [26, 27]. Accordingly, a sample size of 26 participants was estimated.

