## Discussion

HB, which literally means anger syndrome, leads to both somatic and psychological symptoms. The psychological symptoms mainly include an inadequate expression of anger and trait anger, and the somatic symptoms mainly include palpitations, chest discomfort and gastrointestinal disorders [7, 42, 43]. Regarding the causes of HB, a person’s specific disposition, stress from a difficult marital relationship or a serious life crisis can both act as risk factors of HB; enduring negative emotions for a long period of time is known to be a root cause of HB [44].

Patients with HB tend to avoid psychiatric treatment and to rely on treatments that focus only on their physical symptoms [43, 45]. These patients also receive insufficient social support [42]. Despite relatively high levels of self-awareness of HB among these patients [3, 10, 11], they have been unable to receive effective treatment; therefore, further research is needed to develop more effective and acceptable treatments for HB.

This is a pilot study that aims to evaluate the feasibility of acupuncture treatment for HB and to confirm basic information about its effects and safety [46]. In pilot studies, determining feasibility should be the first priority, and data regarding treatment effects should be descriptively analyzed to avoid exaggerated interpretations [47–51]. Therefore, this trial primarily aims to obtain information about the recruitment, consent, and integrity of the study protocol based on recruitment rate, compliance rate, and completion rate. Clinical effects will be assessed to explore the effects and safety of the intervention and to determine the effect size [47, 52, 53]. We will present Cohen’s *d*, which provides an estimated effect size, because the effect size provides numerical information about the actual difference between two outcomes whereas *p* values are affected by sample size and only provide a dichotomous assessment of statistical significance [54–57]. These data will provide the information needed to calculate the sample size as well as information on the intervention effects that can be easily compared to interventions applied in other studies [38, 47].

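### Cohen's d without a stated small-sample correction, at about 13 per arm, overstates any non-zero true effect by about 3% on average; reporting Hedges' g removes this at no real cost

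*Protocol article*

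**What the plan says.** In the protocol article, Statistical analysis names Cohen's d as the effect size for the clinical outcomes and describes it as a quantity "which is an estimated effect size that indicates the standardized difference between two mean values". It is taken at the end of the 4-week treatment. The section does not say which SD is the divisor or whether a small-sample correction is applied.

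The number of participants comes from two places. Sample size calculation says that "a sample size of 26 participants was estimated" and that "the sample size was not decided based on power calculations". Background describes a "parallel-design pilot study using sham-treatment control and a 1:1 allocation". That makes 13 per arm as randomised.

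The effect size has three stated uses:

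- **Acceptability.** Under Feasibility outcomes, acupuncture counts as acceptable for a full-scale study if "the effect size is greater than 0.2 in at least three of six major symptoms".
- **Comparison.** The Abstract and the Discussion say that d will allow comparison with other treatments studied elsewhere.
- **Planning.** The Discussion adds: "These data will provide the information needed to calculate the sample size".

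The Discussion also says that effects in a pilot should be read descriptively, so as not to exaggerate them.

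**The concern.** Cohen's d divides a mean difference by an estimated SD. With few degrees of freedom the reciprocal of that SD is too large on average, so d overstates the true standardized difference by a factor that depends only on the degrees of freedom. This is separate from the width of the confidence interval and from any selection caused by the 0.2 rule.

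The use most exposed is comparison. The Discussion prefers d to p values because p values depend on sample size. The expected value of d also depends on sample size whenever the true effect is not zero: it is inflated in a study of 26 and almost unbiased in a large one. Setting this pilot's d beside effect sizes from larger studies gives the pilot a small built-in advantage, which runs against the article's aim of avoiding exaggeration.

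**Working it through.** The plan has no figure to reproduce here, because 26 was not derived from a significance level, power or effect. The check is of the estimator.

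**Inputs.** From the article: 26 participants, 1:1, Cohen's d, cut-off 0.2 in three of six symptoms. Assumed: between-group d, pooled SD, normal data, equal arms. No dropout rate is given, so smaller arms are shown as a range.

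**Mean bias.** With df = 2n − 2, the expected value of d is the true effect divided by J, where

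J = Γ(df/2) / [√(df/2) × Γ((df − 1)/2)] ≈ 1 − 3/(4 df − 1).

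At 13 per arm, df = 24 and J ≈ 1 − 3/95 = 0.968, so 1/J = 1.033.

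| Analysed per arm | df | J | Mean overstatement of a non-zero effect |
|---|---|---|---|
| 13 | 24 | 0.968 | 3.3% |
| 12 | 22 | 0.966 | 3.6% |
| 11 | 20 | 0.962 | 4.0% |
| 10 | 18 | 0.958 | 4.4% |

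For contrast, a study with 100 per arm has df = 198 and J ≈ 1 − 3/791 = 0.996, an overstatement of about 0.4%. If the divisor were the SD of one arm only (df = 12), J is 0.936 and the overstatement about 7%.

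**Against sampling error (13 per arm).** The bias is the true effect × (1/J − 1):

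- true effect 0: bias 0, sampling SD of d 0.410;
- true effect 0.2: bias 0.0065, SD 0.411, so about 2% of one SD;
- true effect 0.5: bias 0.016, SD 0.417, so about 4% of one SD.

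Multiplying by J removes the mean bias and also shrinks the spread. At a true 0.2 the root mean squared error falls from 0.411 to 0.398.

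**Effect on the 0.2 rule.** Requiring g > 0.2 is the same as requiring d > 0.2/0.968 = 0.2065. From the t distribution (noncentral where the effect is not zero), 13 per arm:

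| True effect | One symptom passes, d | One symptom passes, g |
|---|---|---|
| 0 | 30.7% | 30.2% |
| 0.2 | 50.2% | 49.6% |
| 0.5 | 77.9% | 77.4% |

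For the full three-of-six rule, simulation (60,000 trials per setting, assumed between-symptom correlations 0, 0.5 and 0.8, true effects 0 to 0.5) gives a fall of 0.2 to 1.2 percentage points. With no true effect, the rule is met in 27.0% to 32.7% of trials using d and 25.9% to 32.1% using g.

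**Effect on a later sample size.** Required n is proportional to 1/d², which is strongly non-linear, so the mean of d is a poor guide to the n that would be planned. The median is more informative. At 13 per arm and true effects of 0.2 to 0.8, the median d is 1.011 times the truth and the median g is 0.979 times the truth. The median planned n is then 1/1.011² = 0.98 of the correct value with d (about 2% too small) and 1/0.979² = 1.04 with g (about 4% too large).

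**The case against.** **The article is silent, not wrong.** It never says that d is uncorrected. The formula is a detail that a condensed article commonly leaves to a fuller document, and Cohen's d is a conventional descriptive statistic. This stands in part: there is no error here. But the article does not leave the estimator open. It names Cohen's d and describes it without a correction, whereas the corrected version usually goes by the name Hedges' g. Read as written, the plan yields d.

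**The bias is trivial beside the imprecision.** This stands. An observed d of 0.2 at 13 per arm has an approximate 95% interval of −0.57 to 0.97, and no multiplier changes that. The only case for correcting is that it costs nothing and improves both mean bias and root mean squared error.

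**Nothing is lost.** Means and SDs will be reported at each assessment, so with the group sizes anyone can compute g later. This also stands, and it limits the matter to what this report itself presents and compares.

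**A stronger reading to avoid.** A reader might infer that, because n varies as 1/d², the next trial would be understated by twice the bias, some 6% or more, and lose power. The documents do not support this. The inference puts the average of d into a non-linear formula, and the medians above show an error of about 2% one way with d and about 4% the other way with g. The article says only that the data will inform the calculation, not that the point estimate will be inserted into it.

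**Conclusion.** The point holds as a minor, optional improvement. At 13 per arm, d overstates any non-zero true effect by about 3.3% on average, rising to 4.4% at 10 per arm. The bias is proportional to the true effect, so it is zero if acupuncture does no better than sham, and a single observed d may still lie below the truth. The consequence is a slight tilt in this pilot's favour when its effect sizes are set beside those of larger studies. The acceptability rule is hardly affected, and no claim is made about under-sizing the full-scale trial. These figures rest on a between-group d, pooled SD, normal data and equal arms. The 10-per-arm figure is illustrative, since no dropout rate is stated.

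**What to change.** In Statistical analysis, state that the effect size for each clinical outcome is Hedges' g = d × J, with J ≈ 1 − 3/(4 df − 1) and df taken from the SD actually used as divisor. List uncorrected d beside it if wished. Use g for the 0.2 rule under Feasibility outcomes and for the comparisons announced in the Abstract and the Discussion.

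The cost is one sentence and one multiplication per outcome. Stated effect sizes become about 3% to 4% smaller; an observed d of 0.200 is reported as 0.200 × 0.968 = 0.194 at 13 per arm. The correction does not make the estimates more precise in any way that matters for planning, and should not be presented as if it did.

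### Cohen's d, which drives the go rule, rests on the post-treatment value alone; adjusting for the baseline already collected would make it more precise, though it would not repair the rule

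*Protocol article*

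**What the plan says.** Under Statistical analysis, the article will report means and SDs at each assessment together with Cohen's d, "which is an estimated effect size that indicates the standardized difference between two mean values". It then fixes the value that enters d: "Effect size will be calculated based on the value immediately after the end of the 4-week treatment (visit 10". Neither a change score nor a baseline covariate is named there or elsewhere in the article.

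Under Clinical outcomes: "The outcome measures regarding clinical effect will be assessed at baseline, week 3, week 5, and week 9". The primary measure is the VAS for the "four major somatic symptoms and two major psychological symptoms of HB will be the primary outcome measure". A baseline value of each scored symptom is therefore collected.

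Under Feasibility outcomes, the treatment counts as acceptable for a full-scale study "if the effect size is greater than 0.2 in at least three of six major symptoms". The Discussion adds that the effect data will feed a later sample size calculation and comparisons with other interventions.

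On size, Sample size calculation says "a sample size of 26 participants was estimated" and that "the sample size was not decided based on power calculations but based on the precision of mean and standard deviation (SD"; Background describes a "parallel-design pilot study using sham-treatment control and a 1:1 allocation".

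**The concern.** A difference in post-treatment means contains two kinds of chance variation: variation that arises after randomisation, and whatever difference the arms happened to have at the start, carried forward in proportion to the baseline-to-post correlation. The second part can be removed with data the trial already holds. With very small arms it is not negligible against a threshold of 0.2.

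This d is more than a descriptive figure. It enters a stated go criterion and will be carried into the planning of the next trial. Avoidable noise in it means avoidable error in both uses.

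**Working it through.** **Inputs from the article.** Total 26 (Sample size calculation); 1:1 allocation (Background), hence 26 / 2 = 13 per arm; threshold d > 0.2 in at least 3 of 6 symptoms (Feasibility outcomes). The figure of 26 cannot be reproduced, because no precision target, SD, effect or dropout is given with it. It is taken as stated.

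**Assumptions not in the article.** Baseline-to-post correlation r = 0.3 to 0.7; for the three-of-six rule, multivariate normal scores, correlation 0.5 between symptoms and the same effect on all six; no attrition. Positive d means in favour of acupuncture.

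**Step 1. Precision of the planned d.** Under no effect, SE = sqrt(2/13) = 0.392, so the 95% half-width is 1.96 × 0.392 = 0.77. The chance that one symptom exceeds +0.2 with no effect is 0.31 (t distribution, 24 df).

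**Step 2. The part due to baseline imbalance.** In SD units the baseline imbalance also has SE 0.392. Only r times the imbalance reaches the post-treatment difference, so the carried part has SE r × 0.392. It exceeds +0.2 with probability P(Z > 0.2 / (0.392 r)). At r = 0.6: 0.2 / 0.235 = 0.85, giving 0.20.

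**Step 3. Precision after adjustment.** ANCOVA SE = 0.392 × sqrt((1 − r²) × 23/22), where 23/22 is the cost of the extra degree of freedom. At r = 0.6: 0.392 × sqrt(0.64 × 23/22) = 0.321.

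**Step 4. Effect on the three-of-six rule.** Simulation with 13 per arm, 60,000 trials per setting, the adjusted difference divided by the pooled unadjusted post-treatment SD.

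| | r = 0.3 | r = 0.5 | r = 0.6 | r = 0.7 |
|---|---|---|---|---|
| SE of carried imbalance | 0.118 | 0.196 | 0.235 | 0.275 |
| P(carried part > +0.2), per symptom | 0.04 | 0.15 | 0.20 | 0.23 |
| SE of difference, planned | 0.392 | 0.392 | 0.392 | 0.392 |
| SE of difference, ANCOVA | 0.383 | 0.347 | 0.321 | 0.286 |
| P(rule met), no effect, planned | 0.32 | 0.32 | 0.32 | 0.32 |
| P(rule met), no effect, ANCOVA | 0.32 | 0.29 | 0.27 | 0.24 |
| P(rule met), true d = 0.5, planned | 0.88 | 0.88 | 0.88 | 0.88 |
| P(rule met), true d = 0.5, ANCOVA | 0.89 | 0.90 | 0.92 | 0.94 |
| Null trials where the two verdicts differ | 0.10 | 0.16 | 0.19 | 0.23 |

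Varying the inter-symptom correlation from 0 to 0.7, the null chance of meeting the rule is 0.26 to 0.34 as planned. After adjustment it is 0.25 to 0.32 (r = 0.3), 0.23 to 0.30 (r = 0.5) and 0.17 to 0.27 (r = 0.7).

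**The case against.** **The sentence may only fix the time point.** There are three post-baseline assessments, and the text does not say that d is unadjusted. A separate analysis plan could add a covariate. That is a fair caution. Still, the article defines d as a standardised difference between two means and then says which value enters it. The post-only reading is the natural one, and the go rule depends on it.

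**Nothing is in error.** A post-treatment d is a common and legitimate estimator, the pilot is descriptive by its own account, and the planned means and SDs at each assessment will let readers see any baseline imbalance. All of this stands. A reader might infer bias from the lack of adjustment, but randomisation keeps the planned d unbiased on average. The issue is precision in a single small trial.

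**The risk is easily overstated.** A reader might note that a baseline difference of more than 0.2 SD has probability 2 × 0.305 = 0.61 and take that as the chance of a misleading go. It is not. That figure counts both directions and sits on the baseline scale, whereas the rule looks in one direction and only r times the imbalance carries over. The relevant range is 0.04 to 0.23.

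**Wide baseline spread is not established.** One might argue that the absence of a minimum VAS at entry makes imbalance worse. The article gives no spread, and the working is in SD units, so spread does not enter it.

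**The gain may be small.** At r = 0.3 the SE barely moves and the rule performs almost as before. This also stands.

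**Conclusion.** The point holds as a worthwhile gain in efficiency. The plan leaves baseline out of an effect size that carries a decision, and including it costs almost nothing. With 13 per arm the SE of 0.39 would fall to between 0.38 and 0.29 for r from 0.3 to 0.7. Which estimator is used would change the go verdict in about 16% to 23% of null trials at r = 0.5 to 0.7, and in about 10% at r = 0.3.

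The size rests on an assumed r, which the article does not give, and on 13 per arm with no attrition. It would be wrong to conclude that adjustment repairs the go rule. Most of the risk of a go with no effect comes from setting a point-estimate threshold of 0.2 against arms of 13, and a null pass probability of about 0.24 to 0.32 remains after adjustment (inter-symptom correlation 0.5).

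**What to change.** Define the effect for each scale as the between-group difference at the post-treatment assessment from an ANCOVA with that scale's own baseline as covariate. Fit it within each imputed dataset and combine the results. Divide by the pooled unadjusted SD, so that d stays comparable with other studies, and report it with a 95% CI. State that this d is the one used in the three-of-six rule.

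Apply the same definition to the secondary measures (anger VAS, BDI, SRI-short form, IOME-HB, serum serotonin), all of which have a baseline value. Keep the raw means and SDs at each assessment as planned.

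Fix the wording before any unblinded data are seen, because adjustment added after an imbalance has been noticed would look data-driven. The cost is a sentence of text, a few lines of SAS and one degree of freedom, with no new visit or measurement. The interval will also show how little a point estimate above 0.2 establishes at this size; the threshold itself needs separate attention.
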